### 13 Assessment of Safety and Data Safety Monitoring Plan (DSMP)

#### 13.1 Definitions for Safety Assessment

The following definitions will be used in the assessment of safety:

An *Adverse Event (AE)* is any negative outcome that is undesirable and unintended, resulting from a participant's involvement in a study. These events can encompass various forms of harm, including physical, psychological, social, legal, or economic impacts. For instance, in social-behavioral research, an example of an adverse event could be a breach of confidentiality, where a participant's private information is disclosed to individuals not involved in the research team.

An *Unanticipated Problem (UP)* is defined as an adverse event that meets three specific criteria:

1. **Unexpected Nature:** The adverse event must be unexpected, meaning its nature, severity, or frequency is inconsistent with the known or foreseeable risks described in the research protocol, informed consent documents, or other relevant sources.
2. **Relatedness to Research:** The adverse event must be related or possibly related to participation in the research. This means there is a reasonable possibility that the event was caused by the research procedures.
3. **Increased Risk of Harm:** The adverse event must suggest that the research places subjects or others at a greater risk of harm than previously known. This assessment involves considering whether the event indicates a new risk that was not anticipated based on prior knowledge of the research and its procedures.

*Serious Adverse Event (SAE)* is any adverse event that

- (1) results in death;
- (2) is life-threatening;
- (3) results in inpatient hospitalization or prolongation of existing hospitalization;
- (4) results in a persistent or significant disability/incapacity;
- (5) results in a congenital anomaly/birth defect; or

*Life-threatening* means that the event places the subject at immediate risk of death from the event as it occurred.

*Unanticipated Problem* is defined as an event, experience or outcome that meets **all three** of the following criteria:

- is unexpected; AND
- is related or possibly related to participation in the research; AND
- suggests that the research places subjects or others at a greater risk of harm (including physical, psychological, economic, or social harm) than was previously known or recognized.

*Possibly related* means there is a reasonable possibility that the incident, experience, or outcome may have been caused by the procedures involved in the research

*Unexpected* means the nature, severity, or frequency of the event is not consistent with either:

- the known or foreseeable risk of adverse events associated with the procedures involved in the research that are described in (a) the protocol-related documents, such as the IRB-approved research protocol, any applicable investigator brochure, and the current IRB-approved informed consent document, and (b) other relevant sources of information, such as product labeling and package inserts; or
- the expected natural progression of any underlying disease, disorder, or condition of the subject(s) experiencing the adverse event and the subject's predisposing risk factor profile for the adverse event.

Both the risks listed in Section 4.1 and unknown risks will be monitored as follows:

Information collected as part of this study could reveal symptoms of major depression and suicidal tendencies. All staff will be trained to identify participants who may have acute attacks of anxiety, emotional distress, or suicidal ideation. Throughout the period of interaction with participants, trained staff members will evaluate and be attentive to the emotional state of the participants and lay person therapists. All staff will be trained by the principal investigator in monitoring, evaluating, and reporting any concerns or mental health events. The wellbeing of participants will be assessed in sessions with providers and via validated measures of depression, anxiety, and PTSD provided through the intervention. The wellbeing of lay person therapists will be assessed via supervision sessions with lay person supervisors, study staff supervisors, and the principal investigator [name]. All staff must complete human subject research training offered by Boston University Medical Campus and the Collaborative Institutional Training Initiative (CITI Program). All study staff must also complete the Good Clinical Practice training offered within CITI Program. [name] has completed Good Clinical Practice Training (Principal Investigator Role: What Every New and Seasoned PI Needs to Know about the Conduct and Oversight of Clinical Research conducted by the Clinical Research Resources Office (CRRO) at Boston University, March 10th, 2023, 3.5 hours), and will complete the refresher course as needed. These extensive and required trainings meet NIH requirements for human subject research training. [name] (Principal Investigator of the study, and Licensed Clinical Psychologist) will be available at all times through her direct phone number for questions about participants, as needed, or in case of an emergency. Participants identified as suicidal or severely depressed are provided with information about the most optimal mental health centers or those closest to the participant. In accordance with the Mental Health Law, the confidentiality and voluntariness of going to a mental health center is guaranteed.

If adverse events occur (i.e., events that are harmful to study participants), staff will be trained to complete adverse event descriptions which will then be transmitted electronically to [name] within 24 hours. If the event is a UP, it will be reported to the IRB through the electronic IRB system. As this is a multi-site study, the Principal Investigator will report any internal and external UP to both the local IRBs and the primary IRB, following the required guidelines. Reports will be submitted as soon as possible, but no later than 7 days after the investigator or research staff becomes aware of the incident. Each report will describe the UP and specify any required changes to the research or explain why no changes are needed. If changes are necessary, a separate amendment request will also be submitted, but this should not delay the initial report. Additionally, the Principal Investigator will submit a summary report of all AE, including SAE that are NOT classified as UP, to the IRB through the electronic IRB system during the continuing review and at the time of study closure. A formal report from a data safety monitor will fulfill the requirement for this summary report. The summary will include an analysis assessing whether the overall pattern of events indicates that the research poses a greater risk of harm to subjects or others, considering physical, psychological, economic, or social harm based on the nature and frequency of the events. At the time of enrollment, participants will be reminded that the Informed consent form has information on how to contact the research coordinator and the Principal Investigator at the study site to report any adverse events or any questions or concerns related to the study. Expedited review will be conducted for all events that meet the Office for Human Research Participants (OHRP) 2007 definition of Serious Adverse Events (SAEs; that is, any fatal event, immediately life-threatening event, requires inpatient hospitalization, permanently or substantially disabling event, jeopardizes health, or any congenital anomaly). This also includes any event that a study investigator judges to impose a significant hazard, contraindication, side

Adaptation and assessment of a common element treatment protocol designed to improve mental health in forcibly displaced populations

Version 1, September 17, 2024

effect, or precaution. For the purposes of this study, all SAE will be required to report to the BMC IRB (Boston Medical Center) and research mentors, Drs. [name] and [name], to the Universidad del Pacífico no matter the judgment regarding their relationship to the study. All pertinent information will be reported, including information about the event and its outcome, concomitant medications, the subject's medical history and current conditions, and all pertinent laboratory data. As noted above, reports of SAE will be submitted as soon as possible, but no later than 7 days after the investigator or research staff becomes aware of the incident. The information will be reviewed, and it will be determined if there was any possible relevance to the study interventions.

If at any time during the study, the investigators, mentors, or IRBs judge that the risk to subjects is greater than the potential benefits, they will have the discretion and responsibility to recommend that the study is terminated. We will use meet the Office for Human Research Participants (OHRP) 2007 definition of Serious Adverse Events (SAEs; that is, any fatal event, immediately life-threatening event, requires inpatient hospitalization, permanently or substantially disabling event, jeopardizes health, or any congenital anomaly).

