## 6 Potential Risks and Benefits

### 6.1 Risks

It is unlikely that participants will be at risk of physical harm as a result of the study participation. The primary risks to participants are breach of confidentiality, fatigue or personal discomfort during the intervention sessions or assessments. Participants may find some of the topics addressed during the sessions or some of the questions asked during assessments to be emotionally upsetting and may experience short-term elevations in negative affect during active intervention sessions. As with any study of participants with mental illness, there is always the risk of symptom worsening. The weekly assessment of symptoms throughout the intervention will allow us to closely monitor any changes in the migrant participants and put in action a safety plan, in case of increased severity or suicidality. Weekly meetings with supervisors, who will be closely accompanied by the research team in weekly group meetings, will enable us to timely identify participants whose symptoms are not progressing as expected and to take timely action. At any point in the study if participants exhibit increasing severity of psychiatric symptoms that warrants a higher level of care, they will be referred to the local hospital. If symptoms require immediate medical management, participants’ family members will be contacted and recommended to bring the participant to the hospital emergency room.

Adaptation and assessment of a common element treatment protocol designed to improve mental health in forcibly displaced populations

Version 1, September 17, 2024

Furthermore, participants will be advised to call the hotline 113 to get in touch with counselors from the Peruvian mental health system or the number 106 in case they need an ambulance.

In the case of the provider participants, they may find some of the topics addressed during the sessions to be emotionally upsetting or may experience concern regarding the wellbeing of some participants. As mentioned above, frequent meetings with supervisors, closely accompanied by the research team, will enable us to discuss these concerns, to identify if the symptoms of a participant are not progressing as expected and to take timely action. Also, supervisions will provide with the opportunity to tackle the discomfort that a provider might be experiencing and to find means to alleviate it.

Other measure to be taken to protect the participants against risk are the following:

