### 15.2 Sample Size Determination

The sample comprises  $n = 90$  pilot participants, of which  $n = 60$  will be randomly assigned to the intervention group and  $n = 30$  to a waitlist control. The sample size for pilot participants is based on a method outlined by Viechtbauer. Viechtbauer suggests that for a pilot trial a sample size of  $n = 59$  is sufficient to detect a problem that emerges for 5% of participants.

We expect participant recruitment to be feasible as the PI and colleagues at Universidad del Pacifico have recruited and engaged with over 2,000 research participants in mental health research. For example, for the prior stages of this project we have engaged  $n = 19$  experts and  $n = 29$  migrants.

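### Section 13.1 makes study causation part of the adverse event definition, against the rest of Section 13, and Section 13.2.1 fixes the conclusion of the safety summary in advance

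*Protocol*

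**What the plan says.** Section 13.1 introduces its definitions as those to be used in assessing safety. An adverse event "is any negative outcome that is undesirable and unintended, resulting from a" participant's involvement in a study. A serious adverse event "is any adverse event that" meets one of the listed seriousness criteria, so it carries the same causal condition. An unanticipated problem must, among other things, be related or possibly related to the research.

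The text on handling events, which follows those definitions, is worded differently. The instruction to staff reads: "If adverse events occur (i.e., events that are harmful to study participants), staff will be trained to complete adverse event descriptions". The seriousness list given there is "any fatal event, immediately life-threatening event, requires inpatient hospitalization, permanently or substantially disabling event, jeopardizes health, or any congenital anomaly", and it is adopted a second time: "We will use meet the Office for Human Research Participants (OHRP) 2007 definition of Serious Adverse Events". All serious events go to the review boards "no matter the judgment regarding their relationship to the study", and possible relevance to the intervention is determined after the report.

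On the periodic summary, the same text calls for an analysis of whether the overall pattern of events points to greater risk. The reporting list at the end of Section 13.2.1 says that adverse events, serious ones included, will be summarised at continuing review together with a statement that the pattern does not suggest greater risk than was known before. It offers no alternative wording.

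**The concern.** A causal condition inside the definition means that someone decides on cause before the event is recorded. An event judged unrelated is then not an adverse event, and later review cannot revisit the decision because there is no record to review. This matters here because Section 6.1 concedes the point for the main foreseeable harm: "As with any study of participants with mental illness, there is always the risk of symptom worsening". Participants are enrolled because they have symptoms, so a non-serious deterioration is easily put down to the underlying disorder.

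Two oversight steps depend on the label. The monthly data review in Section 13.2.1 looks at reported adverse and serious adverse events, and the summary to the IRB covers adverse events. What is never classed as one reaches neither.

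The second defect concerns the summary itself. If its conclusion is written before the data exist, the wording does not follow from the analysis that the protocol requires.

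**Working it through.** No arithmetic applies. The protocol gives no figure on this point and the question is one of wording, so the check sets the statements side by side and then follows three kinds of event through them.

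**Step 1. Where does each statement place the judgement of cause?**

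| Place in the protocol | Role of cause |
|---|---|
| Section 13.1, adverse event | Condition of entry |
| Section 13.1, serious adverse event | Inherited from the adverse event definition |
| Section 13.1, unanticipated problem | A separate test applied to an adverse event |
| Section 13.1, meaning of unexpected | The event is compared with the natural course of the participant's underlying disorder |
| Section 13, instruction to staff | None: harmful events |
| Section 13, seriousness list | None |
| Section 13, reporting of serious events | Judged after the report |

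The first two rows conflict with the other five. If every adverse event already results from the study, the relatedness test for unanticipated problems is largely redundant, the comparison with the natural course of the disorder has little to work on, and the rule to report serious events whatever their relationship has almost nothing to act on.

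**Step 2. What happens to an event under each reading?**

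| Event | Section 13.1 read literally | Later text of Section 13 |
|---|---|---|
| Non-serious harm judged related | Adverse event | Adverse event |
| Hospitalisation judged unrelated | Not an adverse event, so not a serious one | Reported as serious |
| Non-serious harm judged unrelated | Not an adverse event | Adverse event under the instruction to staff |

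The readings agree on the first row. On the second, the later rule is explicit and specific, so it probably prevails. On the third, no explicit rule overrides the definition. There is only the looser description given to staff. This row is the practical gap.

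**Step 3. The summary.** The handling text asks whether the pattern indicates greater risk, so the answer may be yes or no. Section 13.2.1 supplies only the answer no. Both describe the summary for continuing review. If the analysis came out yes, the two instructions could not both be followed.

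**The case against.** The strongest reply is that the definition is the outlier and that staff are unlikely to follow it literally. Section 13 trains staff to report concerns and mental health events generally, with no causal condition, and its definition of unexpected contemplates adverse events that follow the course of the disorder. Symptom worsening is also in the data whatever its label: during treatment PCL5 is collected weekly and PHQ9 and GAD7 every two weeks, all three are collected at endline in both arms, and Section 6.1 links symptom monitoring to a safety plan. All of this stands, and it keeps the severity low. It does not remove the contradiction. The scores are outcome data, not adverse event records, and so do not enter the event review or the summary by themselves.

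A reader might infer more than the protocol supports:

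- **That serious events will be lost.** The explicit rule on reporting them makes this unlikely.
- **That event rates will be biased between arms.** Waitlist participants have no sessions to which harm could be attributed before week 12, but Sections 15.1 and 15.3 plan no comparison of adverse events between arms.
- **That the pilot loses a calculable part of its ability to find problems.** Section 15.2 says its sample size "is sufficient to detect a problem that emerges for 5% of participants", but does not tie this to adverse event recording. The protocol gives no share of events that would be judged unrelated, and all 90 participants, not only the first 60, are eventually to be treated. Any figure would rest on invented shares.
- **That a harmful pattern could not reach the IRB.** An unexpected frequency of possibly related events that suggests greater risk can qualify as an unanticipated problem, reportable within 7 days. Safety monitors' reports that recommend changes have the same limit, and Section 13.3 leaves room to recommend termination.
- **That the 7-day report of serious events contradicts the later summary.** The two can be read as cumulative, since Section 13.2.1 presents itself as summarising the procedures before it.

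**Conclusion.** The point holds as a low-severity wording correction to two safety rules. The definition in Section 13.1 contradicts the separate relatedness test in the same section, the cause-free instruction and seriousness list that follow, and the rule on reporting serious events. What is at risk in practice is the recording of non-serious harm judged unrelated. The fixed statement in Section 13.2.1 contradicts the open analysis required earlier in Section 13.

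Neither defect can be sized from the protocol. The conclusion on the first assumes that some staff would apply the formal definition as written; if all follow the instruction given to them, nothing is lost. The conclusion on the second needs no assumption about conduct, because the two sentences disagree on their face.

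**What to change.** 1. In Section 13.1, define an adverse event as any untoward event in a participant after enrolment, regardless of cause, and state that relatedness is judged separately once the event is recorded. The serious adverse event definition then needs no change, and the relatedness test for unanticipated problems regains its purpose.
2. In the reporting list of Section 13.2.1, replace the fixed sentence with a statement on whether the pattern of adverse events, in total, suggests greater risk than previously known, based on the analysis that Section 13 already requires.

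Optional: add one adverse event question to the existing week-12 REDCap form, asked in the same way in both arms.

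The cost is an amendment to two sentences and a few more reported events. The design, sample size and analysis do not change.

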### 13.2.1 Multi-Site Safety Monitoring

In this multi-site study, we have established a comprehensive plan for the coordination of safety monitoring across all participating sites, as described above. The following summarizes the aforementioned procedures on how communication will be managed regarding information relevant to participant protection, including SAE, UP, protocol modifications, and training and compliance.

#### 1. Regular Communication Protocols

- Weekly Team Meetings: The PI and research coordinators from each site will participate in regular weekly meetings to discuss ongoing participant safety, review reported events and address any concerns.
- Monthly Data Review: A systematic review of data will occur monthly, where the research team will evaluate the frequency and nature of reported AEs and SAEs across sites.

#### 2. Inter-Site Communication

- Immediate Notification of SAEs and UPs: Any site that identifies a SAE or UP will notify the PI and all other sites within 24 hours of awareness. This ensures that all sites remain informed of potential risks and can adjust their monitoring practices accordingly.
- IRB Reporting: The PI will ensure that all UPs and SAEs are reported to the appropriate Institutional Review Boards (BMC and Universidad del Pacifico IRB) within the required timeframe, with updates communicated to all sites.

#### 3. Protocol Modifications

- Protocol Amendments: If protocol modifications are necessary based on interim results or safety monitoring, these will be communicated to all sites immediately. Affected sites will receive detailed instructions on implementing changes and will be required to confirm understanding and compliance.

#### 4. Training and Compliance

- All site staff will undergo training on the safety monitoring procedures and communication protocols established for the study. This training will ensure that every team member understands their role in participant safety and the importance of timely reporting.

By implementing these structured communication and coordination plans, we aim to ensure participant safety across all sites while maintaining compliance with regulatory requirements and ethical standards

Adaptation and assessment of a common element treatment protocol designed to improve mental health in forcibly displaced populations

Version 1, September 17, 2024

The Principal Investigator at BMC/BU Medical Campus will report Unanticipated Problems, safety monitors' reports, and Adverse Events to the BMC/BU Medical Center IRB in accordance with IRB policies:

- Unanticipated Problems occurring at BMC/BU Medical Campus and the Universidad del Pacífico will be reported to the BMC/BU Medical Campus IRB within 7 days of the investigator learning of the event.
- Adverse Events (including Serious Adverse Events) will be reported in summary at the time of continuing review, along with a statement that the pattern of adverse events, in total, does not suggest that the research places subjects or others at a greater risk of harm than was previously known.
- Reports from safety monitors with recommended changes will be reported to the IRB within 7 days of the investigator receiving the report.
- Reports from safety monitors with no recommended changes will be reported to the IRB at the time of continuing review.

The Principal Investigators at the Universidad del Pacífico will additionally follow the reporting policies and procedures of their local IRB.

